### Adverse effects and co-medication

To assess the safety of metformin administration, the primary evaluation criteria are the absence of the adverse effects (AEs) described. The patients are assessed regarding all symptoms at each visit to identify potential AEs and the use of co-medication in the previous two months. A contact number is provided to enable enquiries regarding any symptom perceived as adverse. At this number, the patient is informed about what to do in the event of an adverse reaction. They are also requested to suspend the medication. The following information is recorded: description, date of onset and end date, severity, assessment of relation to the study medication, other suspect drug or device and action taken. Follow-up information should be provided as necessary. The prominent AEs are as follow: diarrhea, nausea, blood in the stools, headache, dizziness, general discomfort, sleepiness, cold or flu, pharyngitis, otitis, allergic episode, lactic acidosis, urea increment, hypercreatininemia, hypertransaminasemia and vitamin B_12_ deficiency, as well as any other symptoms reported by the participants. The relationships of the AEs to the study medication will be assessed by a qualified medical investigator.

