### Sample size

As previously indicated, the principal variable is the BMI *Z* score, on which the sample size calculation was based. Its standard deviation is 2.29 in the least favorable case (according to the tables by Cole et al. [29]), and a desired minimum difference of 2 points is expected. With an *α* error of 0.05, a β error of 0.20 and an estimated follow-up loss of 20 %, four groups in total are planned for the study: two groups of obese children (pre-pubertal and pubertal) treated with metformin and two groups of obese children (pre-pubertal and pubertal) treated with a placebo; there is a requirement of at least 40 patients per group (× four groups = 160 children total).

The clinical argument for the choice of the principal variable adheres to the fact that the obesity concept is based on the BMI, as the bibliography endorses. However, it should be noted that the BMI in childhood changes substantially with age [30]. Thus, age- and sex-specific cut-off points are needed to define pathology in children via means of a *Z* score [29] to obtain a more accurate value.

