### Interim analyses and stopping rules

Interim or preliminary analyses during the course of this RCT are not planned. In the event of subject withdrawal, a replacement or substitution is not planned; thus, these participants will be considered lost. The data associated with these subjects will subsequently be excluded from the statistical analysis. For this reason, the calculation of the sample size has included a potential loss of up to 20 %.

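### The rule excluding all data of withdrawn children is not limited to efficacy, so read literally it can drop adverse effects that ended treatment and understate harm

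*Protocol article*

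**What the plan says.** Protocol article, Interim analyses and stopping rules: "In the event of subject withdrawal, a replacement or substitution is not planned; thus, these participants will be considered lost". The next sentence reads: "The data associated with these subjects will subsequently be excluded from the statistical analysis". It gives no reason for withdrawal that would be treated differently and does not restrict the kind of data. The same paragraph uses this rule to justify the attrition allowance, which the Sample size section gives as "an estimated follow-up loss of 20" per cent.

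Protocol article, Adverse effects and co-medication: a child with an adverse reaction is told by telephone what to do, and of these families the article says "They are also requested to suspend the medication". For safety, "the primary evaluation criteria are the absence of the adverse effects (AEs) described". The list that follows includes gastrointestinal complaints and lactic acidosis, but also "headache, dizziness, general discomfort, sleepiness, cold or flu, pharyngitis, otitis, allergic episode", and closes with "as well as any other symptoms reported by the participants". Dates, severity, relation to study drug and action taken are recorded for each event.

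Protocol article, Adherence and tolerance: adverse effects are summarised descriptively according to the dose reached. The children included are not stated, and no contrast between metformin and placebo is named.

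**The concern.** For efficacy, dropping withdrawn children is a question of missing outcome data. For safety it is different, because the adverse effect can be the cause of the withdrawal. A child who stops for diarrhoea and then leaves the trial has already supplied the relevant safety observation, and the exclusion rule as worded would discard it. One consequence needs no assumed rate: among the children left after exclusion, the proportion who stopped for an adverse effect and withdrew is zero in both arms, whatever happened.

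The stake is the comparison of harm in a placebo-controlled phase III trial of a new indication in children aged 7 to 14. If children who cannot tolerate the drug leave the analysis set, metformin can look closer to placebo than it is.

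The safety criterion does not repair this. It fixes no unit, threshold or comparison. Read per child, as free of listed effects or not, it gives a cold the same weight as lactic acidosis, so background illness in both arms dilutes any drug signal.

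**Working it through.** **Inputs from the article.** 160 children, half assigned to each treatment (Sample size; Randomization), so N = 80 per arm. Planned loss L = 20%, so 0.20 × 80 = 16 lost and 64 kept per arm. The article states no adverse-event rate and no rate of withdrawal after an event, so there is no safety figure of the plan to reproduce.

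**Assumed inputs.** 24/80 metformin children (30%) and 12/80 placebo children (15%) have a given adverse effect. A fraction f of the affected children withdraws, the same f in both arms. Total loss is 20% in each arm.

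**Step 1, all treated children.** 30.0% − 15.0% = +15.0 points. Wald 95% interval: 15.0 ± 1.96 × √(0.30 × 0.70/80 + 0.15 × 0.85/80) = 15.0 ± 12.7, that is 2.3 to 27.7.

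**Step 2, after exclusion.** The proportion seen in an arm with true proportion p is p(1 − f)/(1 − L). With the same f and L in both arms, the difference is multiplied by (1 − f)/(1 − L). It shrinks when f exceeds L, is unchanged when f equals L, and grows when f is below L.

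| Loss per arm | f | Metformin | Placebo | Difference (95% CI), points |
|---|---|---|---|---|
| 20% | 0.20 | 30.0% | 15.0% | +15.0, no bias |
| 20% | 1/3 | 16/64 | 8/64 | +12.5 (−0.9 to 25.9) |
| 20% | 1/2 | 12/64 | 6/64 | +9.4 (−2.6 to 21.3) |
| 10% | 1/6 | 20/72 | 10/72 | +13.9 (0.8 to 27.0) |
| 10% | 1/3 | 16/72 | 8/72 | +11.1 (−0.9 to 23.2) |

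**Step 3, sensitivity to the equal-loss assumption.** Fixing 16 losses per arm makes unaffected children withdraw at different rates. At f = 1/2 it is 4 of 56 on metformin and 10 of 68 on placebo. Suppose instead that 32 of 160 are lost in total and unaffected children leave at one common rate:

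- f = 1/3: 12 affected children leave, so 20 of the 124 unaffected leave (16.1%). Metformin 16/(16 + 47.0) = 25.4%, placebo 8/(8 + 57.0) = 12.3%, difference +13.1.
- f = 1/2: 18 affected children leave, so 14 of 124 unaffected leave (11.3%). Metformin 12/(12 + 49.7) = 19.5%, placebo 6/(6 + 60.3) = 9.0%, difference +10.4.

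The direction is the same and the shrinkage slightly smaller.

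**The case against.** The strongest reply is that the exclusion sentence was meant for efficacy. It stands beside the no-replacement rule and the 20% allowance, the sample size rests on BMI *Z* score alone, and the Statistical analysis section just before it names no adverse-event analysis. Adverse effects have their own descriptive report under Adherence and tolerance, indexed to the dose reached, which leaves room for children who did not keep the full dose. A safety population is often defined in a fuller document not shown here.

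Much of this is fair. It makes the efficacy-only reading plausible, but the text does not state it, and the tolerance report neither says that withdrawn children are kept nor compares the arms. The point therefore rests on a rule that is written down, not on a missing definition. Case-level safeguards (recorded severity and causality, emergency unblinding, reports to the Ethics Committee) protect individual children but do not return excluded children to a comparison of arms.

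Two stronger readings are not supported:

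- A reader might infer that every child who suspends medication is excluded. Suspension is not withdrawal, and the article does not equate them.
- A reader might infer that the safety criterion can never be met, since some child in an arm of 80 will catch a cold. That needs absence across a whole arm, which the article does not require. Read per child, the criterion can be met and compared with placebo. The open-ended list is sound practice for collecting events.

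**Conclusion.** The concern stands as a possible bias created by an unrestricted rule. Under the assumed 24/80 against 12/80 and 20% loss per arm, a true difference of +15.0 points would appear as +12.5 if a third of affected children withdrew and +9.4 if half did. In both cases the interval would come to include zero. If affected children withdraw at the overall 20%, nothing is lost but precision. Every event and withdrawal rate here is an assumption, so the figures show what could happen and do not forecast the trial's result. The bias requires that the rule is applied to safety data and that affected children withdraw more often than the overall loss rate.

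The *absence* criterion is loosely phrased rather than unattainable. Its weakness is that it merges trivial and serious events and fixes no comparison.

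**What to change.** Add one sentence to Interim analyses and stopping rules: the exclusion of withdrawn children does not apply to safety data. In Adverse effects and co-medication, replace the *absence* criterion with a by-event summary in all treated children, including those who suspend medication or withdraw. For each event it should give the proportion of children affected by arm, all-cause and judged related, and the metformin-placebo difference with a 95% confidence interval. State the shorter follow-up of withdrawn children beside these proportions.

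The cost is wording. Symptoms are already recorded at each visit, with a contact number between visits, so events up to withdrawal should be on file. No change in sample size follows. Recruitment was continuing when the article was written, and the blind is to be kept until the analyses are complete, so the change can be made without knowledge of results. The limit is precision: with 80 per arm and equal rates, the interval half-width is 1.96 × √(2p(1 − p)/80), or 12.4 points at 20% and 15.2 points at 40% or 60%. Only large differences in harm could be shown.

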### Outcome measures

#### Anthropometry

Body weight (kg), height (cm) and waist circumference (cm) are measured via standardized procedures. The BMI and BMI *Z* score are calculated based on Spanish reference standards published by Sobradillo et al. [31]. Obesity is defined according to the BMI, with the age and sex-specific cut-off points proposed by Cole et al*.* [29] (BMI >95th percentile). Anthropometric measurements are obtained by a single examiner with the children barefoot and in their underwear. To obtain data on body composition, fat mass, lean mass and total body water are measured via bioimpedance technology using Tanita B18.

#### Biochemical analysis

The serum concentrations of glucose, lipids (total cholesterol, triglycerides (TG), high-density lipoprotein cholesterol (HDLc), and low-density lipoprotein cholesterol (LDLc)), apolipoprotein A1 (Apo-A1) and apolipoprotein B (Apo-B) are analyzed via spectrophotometry or a chemiluminescent microparticle immunoassay (CMIA) to measure the insulin concentration, according to auto-analyzers with standardized methods and both intra- and inter-laboratory control using internal and external quality control programmers at the Clinical Analysis Laboratory of each hospital. The Quantitative Insulin Sensitivity Check Index (QUICKI) and the homeostasis model assessment for insulin resistance (HOMA-IR) are calculated using the fasting plasma glucose and insulin values:$$ \begin{array}{l}\mathrm{HOMA}=\mathrm{Fasting}\ \mathrm{insulin}\ \left(\upmu \mathrm{U}/\mathrm{ml}\right)\times \mathrm{fasting}\ \mathrm{glucose}\ \left(\mathrm{mmol}/\mathrm{l}\right)/22.5\\ {}1/\left(\mathrm{Log}\ \mathrm{fasting}\ \mathrm{insulin}\ \left(\upmu \mathrm{U}/\mathrm{ml}\right)+ \log\ \mathrm{fasting}\ \mathrm{glucose}\ \left(\mathrm{mg}/\mathrm{dl}\right)\right)\end{array} $$

#### Inflammation and cardiovascular risk biomarkers

Specific biomarkers of inflammation and cardiovascular risk, including adiponectin, leptin, resistin, myeloperoxidase (MPO), plasminogen activator inhibitor-1 (PAI-1), tumor necrosis factor-alpha (TNF-α), monocyte chemoattractant protein-1 (MCP-1), interleukin-6 (IL-6), interleukin-8 (IL-8), soluble intercellular adhesion molecule-1 (sICAM-1), soluble endothelial selectin (sE-Selectin) and soluble vascular adhesion molecule-1 (sVCAM-1) are analyzed in duplicate on a Luminex 200 system with the XMap technology (Luminex Corporation, Austin, TX, USA) and using human monoclonal antibodies (Milliplex Map Kit, Millipore, Billerica, MA, USA).

#### Oxidation biomarkers

The plasma total antioxidant capacity (TAC) is assessed with a spectrophotometric commercial antioxidant assay kit (Cayman, Ann Arbor, MI, USA), which is based on a colorimetric reaction. The oxidized LDL (Cayman, Ann Arbor, MI, USA), as well as the oxidative stress biomarkers isoprostane (Oxford Biomedical Research, Oxford, UK) and 8-hydroxy-2-deoxyguanosine (JaICA (Japan Institute for the Control of Ageing), Fukuroi, Shizuoka, Japan) are determined in duplicate via enzyme-linked immunosorbent assay (ELISA) in urine using a microplate reader BioTeK synergy HT.

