## Methods

### Objectives

In accordance with the previously discussed background, the present study has four main objectives: the first objective is to determine the efficacy of metformin in combination with a lifestyle intervention in reducing BMI in obese children compared with placebo after 6 months; the second objective is to evaluate the effects on insulin resistance inherent to metabolic syndrome; the third objective is to identify its effects on inflammatory, cardiovascular risk and oxidative stress biomarkers; the fourth objective is to evaluate the change of gut microbiota composition after treatment. Additionally, metformin differential response will be analyzed according to genetic polymorphisms in drug uptake transporter genes.

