### Blood, urine and fecal sampling

General biochemical analyses are performed at the participating hospitals following internationally accepted protocols.

Blood samples are obtained for biochemical and hematological screening tests between 08.30 and 10.30. Three milliliters of blood are collected at the beginning and at the end of the trial. The blood is drawn via the antecubital vein. Peripheral white blood cells (buffy coat) are taken for deoxyribonucleic acid (DNA) extraction. Moreover, a 1-ml urine sample is obtained for oxidation marker analysis. Children should not eat for 12 hours before the sampling. All samples are collected and stored frozen by the research staff. The samples will be analyzed in the clinical laboratory of each hospital, as well as the INYTA.

In order to studying the childrens’ gut microbiota, 100–200 g of fecal sample is collected in a sterile container by parents at the beginning and at the end of the trial. Immediately, all samples are stored frozen until to be analyzed at the INYTA.

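### As written, oxidized LDL is assigned to an ELISA in urine; the specimen should be corrected to plasma, and the expression of the two urinary markers stated

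*Protocol article*

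**What the plan says.** The Oxidation biomarkers section of the protocol article has two sentences on specimen and method. The first covers one marker: "The plasma total antioxidant capacity (TAC) is assessed with a spectrophotometric commercial antioxidant assay kit". The second opens with "The oxidized LDL (Cayman, Ann Arbor, MI, USA), as well as the oxidative stress biomarkers isoprostane", adds 8-hydroxy-2-deoxyguanosine, and ends by saying that these "are determined in duplicate via enzyme-linked immunosorbent assay (ELISA) in urine using a microplate reader". Urine is the only specimen that the second sentence names.

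The section Blood, urine and fecal sampling states that "a 1-ml urine sample is obtained for oxidation marker analysis", without saying which markers are meant. It also states: "Children should not eat for 12 hours before the sampling". It describes no timed urine collection and does not mention fluid intake.

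These markers belong to a main objective. Under Objectives, "the third objective is to identify its effects on inflammatory, cardiovascular risk and oxidative stress biomarkers". They do not drive the design. Under Sample size, "the principal variable is the BMI *Z* score, on which the sample size calculation was based".

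**The concern.** LDL is a lipoprotein particle that circulates in blood, and the article itself measures LDL cholesterol in serum (Biochemical analysis). Table 2 excludes children with any previous underlying disease, so leakage of such particles into urine is not expected. A laboratory that followed the Oxidation biomarkers section to the letter would obtain oxidized LDL values that say nothing about the child's oxidative status. One of the four oxidation markers under the third main objective would then be lost.

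The secondary question concerns isoprostane and 8-hydroxy-2-deoxyguanosine, for which urine is a legitimate specimen. The concentration of any urinary analyte depends on how dilute the urine is as well as on how much is excreted. The article does not say whether results are expressed per creatinine, per another dilution measure, or as raw concentrations. How they are expressed is part of the definition of these two endpoints.

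**Working it through.** The plan gives no figure for this point, so there is none to reproduce. The main check is a reading of the text.

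**Specimen stated for each marker (Oxidation biomarkers)**
- TAC: plasma, stated.
- Oxidized LDL: first subject of the second sentence; urine is the only specimen named.
- Isoprostane: same sentence, urine.
- 8-hydroxy-2-deoxyguanosine: same sentence, urine.

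The second sentence has one verb, one method and one specimen for three analytes. The sentence before it names plasma, so the section does distinguish between specimens. The sampling section does not resolve the matter, because it collects urine for oxidation markers in general. No other section gives a specimen for oxidized LDL. The literal reading is therefore urine.

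**Dilution of the two urinary markers**
- Stated: a 1-ml sample and 12 hours without food.
- Not stated: timed collection, urinary creatinine, specific gravity, or how results are expressed.
- The fixed effects listed under Statistical analysis contain no dilution term.
- Nothing says that results are analysed uncorrected.

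**Illustration on assumed values only.** The article gives no variance for these markers or for urine dilution. Assume log-scale SDs between 0.3 and 0.7 for both the dilution-free marker (SD_m) and dilution (SD_d), and assume that the two are independent.
- Share of variance due to dilution = SD_d² / (SD_m² + SD_d²).
- Lowest: 0.3² / (0.7² + 0.3²) = 0.09 / 0.58 = 16%.
- Equal SDs: 50%.
- Highest: 0.7² / (0.3² + 0.7²) = 0.49 / 0.58 = 84%.

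For power, take 160 × 0.80 / 2 = 64 completers per arm and an effect that would have 80% power with no dilution noise. With dilution noise, power = Φ(2.80 × √(1 − share) − 1.96).
- Share 16%: Φ(2.80 × 0.919 − 1.96) = 73%.
- Share 50%: Φ(2.80 × 0.707 − 1.96) = 51%.
- Share 84%: Φ(2.80 × 0.394 − 1.96) = 20%.

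The range is so wide that it settles only the direction: uncorrected dilution lowers power. Dilution exceeds half of the variance only where its assumed SD is larger than the marker's. The calculation also treats correction as perfect, so it shows the most that correction could recover.

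**Number of creatinine assays.** 160 children × 2 time points = 320 at most, if urine is taken at baseline and at the end, as blood is.

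**The case against.** On oxidized LDL, the fair defence is that the sentence is a merged list. Its construction sets the last two analytes apart as the oxidative stress biomarkers, so the closing reference to urine may have been meant for those two alone. Blood is drawn at both time points and plasma is already used for TAC, so laboratory practice may well be sound. That is plausible, and the article cannot show what the laboratory does. It does not remove the need for correction: the specimen is stated, and as stated it is wrong.

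On dilution, the defence is stronger. This is a condensed article, and normalisation of urinary results is commonly left to the full protocol, the laboratory manual or the analysis plan. The assay description is visibly incomplete: raised urea, creatinine and transaminases and vitamin B12 deficiency are listed as adverse effects, yet Outcome measures describes no assay for any of them. The absence of urinary creatinine from the text therefore does not show that it is not measured. This objection stands, and it reduces the dilution point to a request for clarification.

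A reader might go further and infer that metformin, through diarrhea and nausea, concentrates the urine and so raises the urinary markers in that arm. The article lists these symptoms as possible adverse effects but gives no frequencies by arm and nothing on urine concentration at month 6. In a randomized, blinded comparison, dilution unrelated to treatment adds noise and does not bias the contrast.

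**Conclusion.** The point holds for the specimen. As written, oxidized LDL is assigned to a urine assay in which it would be uninformative in this population. That conclusion rests on the literal reading of one sentence and on the ordinary physiology of a circulating lipoprotein in children without underlying disease. It affects one of four oxidation markers, none of them the principal variable.

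For isoprostane and 8-hydroxy-2-deoxyguanosine, the article leaves their expression open. A reader might conclude that the oxidative stress endpoints largely measure urine concentration, or that a given fraction of the children is effectively lost. The documents do not support either: they do not say that results are left uncorrected, they give no variances, and TAC is measured in plasma and is untouched. If correction is in fact absent, the main effect is added noise of unknown size. TAC, the BMI Z score and the sample size are unaffected.

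**What to change.** 1. Amend the second sentence of Oxidation biomarkers so that oxidized LDL is measured in the plasma sample already used for TAC, with urine applying only to isoprostane and 8-hydroxy-2-deoxyguanosine. If the laboratory already works this way, this is a change of wording only. If not, confirm that enough stored plasma remains from the 3-ml blood draw.
2. State how the two urinary markers are expressed. If the full protocol does not already provide for correction, measure creatinine in the same stored 1-ml aliquot and analyse both markers per creatinine. The log concentration with log creatinine as a covariate could serve as a sensitivity analysis.

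The second step costs at most 320 routine assays and needs no further sample from any child. Recruitment was continuing at the time of the article and samples are stored frozen, so part of each aliquot should be reserved for creatinine before the ELISAs use it up.
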